## Results

Forty patients will be included (8 patients in each center), that is, 60 consultation observations (2 consultations per patient in the intervention groups given the modalities of the SDM process) will be conducted in 2025. Eight focus groups will be conducted in the 5 centers (2 groups in each intervention CFRC and 1 group in each control CFRC) in 2025. This qualitative corpus plus responses to the patient and physician questionnaires will make it possible to know whether the practice of SDM in CFRCs is increased by an implementation strategy and to analyze the experience of patients and their relatives regarding decision-making modalities. Analysis of the outcomes and experience of the implementation of SDM are of importance to identify the facilitators and barriers to SDM from patients’ and CFRCs’ point of view.

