### Design and Setting of the Study

Based on our previous work on SDM in cystic fibrosis [21] and the Consolidated Framework for Implementation Research of Damschroder et al [32], this quasi-experimental here-elsewhere study compares the populations of 3 centers receiving the intervention with those of 2 centers not receiving it (controls). The 5 centers will be studied simultaneously to reduce the risk of contamination of the control group. The evaluation will follow a mixed methods approach, combining qualitative methods (consultations observations, individual semistructured interviews with patients, and focus groups with health care professionals) with quantitative methods (self-administered questionnaires). A convergent mixed methods approach will be used, with concomitant data collection, separate analysis, and subsequent linking of results. This study conforms to the StaRi (Standards for Reporting Implementation Studies) checklist (Multimedia Appendix 1).

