### Visit V1

In the CFRCs of the control group, the physician will present the patient with information on diabetes management according to his or her usual practice. In the CFRCs in the intervention group, the physician will present the patient with information on diabetes management according to SDM (options, benefits, and risks) by using the information and decision support tool. The patient will be “activated” prior to the consultation, inviting him/her to ask questions using the “Ask 3 questions” tool. During the V1 visit for the control and intervention groups, the investigator will fill in the patient’s clinical data and SDM-Q-9 adapted to the physician immediately after the consultation. The patient fills in the questionnaires immediately after the consultation (the questionnaires are handed over by the methodologist or a member of the CFRC). The methodologist in social sciences will observe the physician-patient interaction during the consultation and complete the OPTION questionnaire; conduct an individual semistructured interview with the patient immediately after the consultation; ensure that the patient completes the SURE, CollaboRATE, SDM-Q-9, and Spielberger State-Trait Anxiety Inventory questionnaires (if the patient does not read French, the methodologist will read the questionnaires to the patient and fill them in with his/her agreement); and collect the patient’s sociodemographic characteristics.

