### Data Collection and Analysis

#### Sample Size

As this is a pilot study, 40 patients will be included and interviewed over a 12-month period. The number of patients included corresponds to the active patient file of the 5 CFRCs over the 12-month inclusion period. Five physicians (1 in each center) will be involved in this study.

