### Statistical Methods

#### Descriptive Analysis

A descriptive analysis of the characteristics of the patient population included (age, sex, history and severity of disease) and of the health care professionals on the CFRC teams (physicians, nurses, dietitians, psychologists, physiotherapists, etc, age, sex, profession, previous training in SDM) will be performed in the 2 study groups. Quantitative characteristics will be described by mean and standard deviation or by quartiles and minimum and maximum values depending on the shape of the distribution. Qualitative characteristics will be described by the numbers and percentages in each category. The comparability of the characteristics will be checked using the chi-square test for qualitative variables and the Wilcoxon test for quantitative variables. Data on the implementation of SDM in the intervention group will also be the subject of a descriptive analysis on the proportion of patients with at least one SDM consultation and the proportion of patients with 2 SDM consultations.

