#### Analysis: Primary End Point

Adoption of SDM as perceived by the patient and measured using SDM-Q-9 will be analyzed in patients with no missing data on this criterion, although an approach to managing missing data may be considered. The frequency distribution of the 6 modalities of SDM-Q-9 will be described for each group in the patient unit. A total score will be obtained by summing the scores for each of the 9 questions. A transformation will be applied to obtain a total score between 0 and 100, with 0 indicating nonadoption of SDM as perceived by the patient and conversely 100 indicating adoption of SDM as perceived by the patient. The total score will be described in each group by mean, standard deviation, median, quartiles, and range, and will be compared between the 2 groups with a nonparametric Wilcoxon test. For patients in the intervention group, the variation in the responses to each of the SDM-Q-9 questions between the 2 consultations will be tested using the McNemar test (test adapted to paired data). Total SDM-Q-9 scores between the 2 consultations will be compared using the Wilcoxon signed-rank test. The same analysis will be performed on the health care professional unit to compare the adoption of SDM as perceived by the health care professional. Discordances between patient and health care professional responses to each of the 9 questions on SDM-Q-9 will be described and tested using the McNemar test. The total SDM-Q-9 score obtained on the patient unit and the professional unit will be compared using the Wilcoxon signed-rank test.

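### Three trained versus two untrained non-randomised centres, with no SDM score before training, can show whether SDM scores differ between them, not that the strategy increased SDM

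*Protocol article*

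**What the plan says.** The Results section, and the Abstract in the same terms, state that the qualitative material together with the questionnaires "will make it possible to know whether the practice of SDM in CFRCs is increased by an implementation strategy".

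The design behind that statement is as follows.

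- **Design and Setting of the Study:** a quasi-experimental study that "compares the populations of 3 centers receiving the intervention with those of 2 centers not receiving it (controls"). No random allocation is described.
- **Sample Size:** 40 patients, a number that follows from feasibility: "The number of patients included corresponds to the active patient file of the 5 CFRCs over the 12-month inclusion period". Also, "Five physicians (1 in each center) will be involved in this study". The Results section gives 8 patients per centre.
- **Standard Care:** decision-making procedures differ by centre and by clinician.
- **Visit V1 and Decision-Making Visit (V2):** the SDM measures are collected at these two visits only. For the patient forms, "The patient fills in the questionnaires immediately after the consultation". In intervention centres V1 is already conducted as an SDM consultation with the decision aid.
- **Analysis: Primary End Point:** the total SDM-Q-9 score "will be compared between the 2 groups with a nonparametric Wilcoxon test".
- **Descriptive Analysis:** characteristics are summarised by group, and then "The comparability of the characteristics will be checked using the chi-square test for qualitative variables and the Wilcoxon test for quantitative variables".

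The limitations paragraph of the Discussion names the small number of centres as a limit on generalisability, and slow recruitment. It does not mention confounding.

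**The concern.** An increase attributed to a strategy needs either a measurement before the strategy or a comparison group that would have scored the same without it. This study has no earlier SDM score in any centre. Its comparison group consists of two centres whose decision-making, by the protocol's own account, is specific to them.

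Centre and physician coincide, and both lie wholly within one group. A physician who already shared decisions well before training would raise the intervention mean in the same way as a successful training programme.

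The stake is the reported conclusion. The Abstract looks ahead to routine use of SDM at national level. A difference that was there before training could be cited as evidence for that step. The same holds for the secondary objective on anxiety, because anxiety is measured only after the consultations.

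**Working it through.** **1. Group sizes.** 5 centres × 8 patients = 40, which reproduces the stated total. Intervention: 3 × 8 = 24. Control: 2 × 8 = 16. The article gives no significance level, power, effect size or SD, so a two-sided 5% level and normal data are assumed below.

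**2. Is any SDM score available from before training?**

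| Source | When | SDM score before training? |
|---|---|---|
| SDM-Q-9 (patient, physician), CollaboRATE, OPTION | V1 and V2 | No; V1 in intervention centres is already an SDM consultation |
| V1 versus V2 comparison, intervention group | Both visits after training | No |
| Team focus group at study start | Intervention centres only | No; qualitative |
| Institutional questionnaire and telephone interview | Study start | No; concerns hospital initiatives |

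A before-after change cannot be calculated in either group.

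**3. How sensitive are the baseline tests?** For a continuous characteristic with imbalance d (in SD units), the normal approximation is

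power ≈ Φ( d / √(1/16 + 1/24) − 1.96 ), with √(1/16 + 1/24) = √0.1042 = 0.323.

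For d = 0.5: 0.5 / 0.323 = 1.55; 1.55 − 1.96 = −0.41; Φ(−0.41) = 0.34.

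| Imbalance | Normal approximation | Simulated Wilcoxon (10,000 runs) |
|---|---|---|
| 0.3 SD | 15% | 14% |
| 0.5 SD | 34% | 31% |
| 0.8 SD | 70% | 65% |
| 1.0 SD | 87% | 83% |

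A 0.5 SD imbalance goes undetected in about 1 − 0.31 = 69% of studies. By the approximation, 80% power needs an imbalance of (1.96 + 0.84) × 0.323 = 0.90 SD.

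For a binary characteristic the approximate power is 23% for 30% versus 50%, 46% for 30% versus 60%, and 91% for 25% versus 75%.

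**4. What do ordinary centre differences do to the primary test?** Scores were simulated with no intervention effect, a random centre effect, 3 versus 2 centres of 8, and the planned patient-level Wilcoxon test. The intraclass correlation (ICC) is assumed, because the article gives none.

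| Assumed ICC | Proportion significant at 5% |
|---|---|
| 0 | 4.5% |
| 0.05 | 8.8% |
| 0.10 | 13.4% |
| 0.20 | 20.8% |
| 0.30 | 26.5% |

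This simulation treats centre effects as unrelated to which centres were trained. Nothing in a non-randomised design guarantees that, so a systematic difference would come on top.

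**5. How much do five centres carry?** There are C(5,2) = 10 ways to pick the two control centres. The smallest centre-level permutation p-value is 1/10 = 0.10 one-sided, or 2/10 = 0.20 when doubled. Neither reaches 0.05.

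**The case against.** **The comparison has concurrent controls, and the label is open.** The five centres are studied simultaneously, the primary objective is already worded as a comparison with usual practice, and the article calls itself quasi-experimental and a pilot. This stands. A reader might infer that the comparison is worthless, and the documents do not support that: a difference between trained and untrained centres can be estimated. What is not supported is the step from that difference to an increase caused by the strategy.

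**The claim rests on qualitative data too.** The sentence covers the whole corpus, including focus groups at the start and end in intervention centres. These can describe context and perceived change. They do not give an SDM score before training, and the control centres have only one focus group each.

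**The baseline check is more than a p-value.** Characteristics are also described by group, so an imbalance will be visible. A reader might infer that the tests will miss any real imbalance, or that a non-significant result will be declared as comparability. Neither holds. The tests would usually find a 1 SD imbalance, and the article does not say what follows from a non-significant result.

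**Adjustment may sit in an analysis plan that is not shown.** This is fair, and its absence from the article is not counted as an error here. It would not rescue the causal sentence either. Covariates cannot separate the strategy from five centres with one physician each, and no analysis can supply a score that the visit schedule does not collect.

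**A baseline anxiety score at V0 might seem an easy repair.** It would be new data collection at a visit the methodologist is not described as attending. V0 follows the glucose test and is run by a physician who, in intervention centres, may already be trained. It is not asked for.

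**Conclusion.** The point holds as a mismatch between the stated conclusion and the design. The study can show whether SDM scores differ between trained and untrained centres. It cannot show that the strategy increased them, because existing centre and physician differences are inseparable from the strategy and no score precedes training. This part needs no numerical assumption.

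The baseline tests will often, not always, miss a moderate imbalance: power is about 31% at 0.5 SD and about 83% at 1 SD, for 24 versus 16 patients, a two-sided 5% level and normal data. The false-positive rate of about 9% to 21% depends on the assumed ICC range of 0.05 to 0.20.

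The matter should be corrected. It does not call for a redesign of a declared pilot.

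**What to change.** 1. **Conclusion and limitations.** In the Abstract and the Results, replace the clause on an increase with: *whether SDM scores differ between trained and untrained centres*. In the Discussion, add that centre and physician differences existing before training cannot be separated from the strategy. Treat the post-consultation anxiety difference as descriptive.
2. **Descriptive Analysis.** Replace the chi-square and Wilcoxon comparability tests with standardised differences between groups and summaries by centre, including the professionals' earlier SDM training, which is already recorded.
3. **Primary end point.** Beside the crude comparison, report as a secondary exploratory result a difference adjusted for two or three pre-specified characteristics already collected (age, sex, disease severity). State that this does not remove centre-level confounding. Forty patients will not support a longer list.

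The cost is a more modest conclusion and a little more analysis. No new data are needed, so the changes remain possible after recruitment has begun.

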## Discussion

This is the first study protocol on cystic fibrosis treatment in France, which is designed to train health care professionals on SDM and implement and evaluate the outcomes of the SDM approach. Training materials and health care professionals trained in SDM could boost SDM implementation in cystic fibrosis therapy in French-speaking countries, where the so-called clinical champions in SDM are needed. Moreover, patients experiencing SDM could support and participate in the SDM acculturation process.

The aim of our study is also to propose an original study based on mixed methods combining quantitative and qualitative analyses by using validated evaluation tools (particularly in French) and to conduct the study with patients and health care professionals for whom the potential benefits are multiple: to support in decision-making concerning diabetes treatment; to improve communication between physicians, health care team, and patients; to improve the quality of experience of the decision-making steps; and to acculturate health care professionals to SDM and formalize their practice, thanks to SDM training.

The protocol and information and the decision support tool developed could serve as a basis for other situations in the field of cystic fibrosis, as in the case of lung transplantation, subject to the adaptations to be made. There are many opportunities for SDM in cystic fibrosis, but little is known about patients’ experience of SDM [42]. The training materials and the teams already trained could prove to be the key to future success, with those trained becoming trainers for other centers. International comparisons could also be developed, notably within the framework of the La Collaboration Francophone sur la Prise de Décision Partagée FREeDOM (French collaboration on SDM), which brings together health care professionals, patients, researchers, and public decision makers, notably from Quebec, Switzerland, Belgium, and France, interested in adapting the approach developed to their countries/context.

Although this is the first French study to train health care professionals and implement and evaluate SDM in cystic fibrosis treatment, compared to the usual clinical practice, the number of CFRCs involved is limited, which will potentially limit the generalizability of the results obtained. This study will nonetheless be conducted at the national level. In addition, only a small number of patients with cystic fibrosis are concerned about the development of diabetes, which could impact the duration of our project in order to obtain the desired number of patients.

## Appendix

Multimedia Appendix 1 StaRi (Standards for Reporting Implementation Studies) checklist.

## Abbreviations

CFRC: cystic fibrosis reference center
FREeDOM: French collaboration on shared decision-making
MAGIC: Making Good Decisions in Collaboration
OPTION: Observing Patient Involvement in Shared Decision Making
SDM: shared decision-making
SDM-Q-9: 9-item Shared Decision-Making Questionnaire
StaRi: Standards for Reporting Implementation Studies
SURE: Sure of myself, Understand information, Risk-benefit ratio, Encouragement
